## Abstract

**Background:**

Exhaustion and fatigue are commonly experienced by parents during the post-partum period, and can have implications for daily functioning, mental health and parenting practices. There is a need for the development of effective interventions to assist parents with the management of fatigue. This paper outlines the procedure for a randomised controlled study which aims to test the efficacy of *Wide Awake Parenting*, a program for the management of fatigue in the postnatal period.

**Methods/design:**

Parents with an infant less than 6 months of age, and from seven Local Government Areas in Melbourne, Australia were invited to participate in this study. Parents were randomised to receive the *Wide Awake Parenting* program (intervention groups) or usual care (control group) offered by health services. The *Wide Awake Parenting* program provides parents with psycho-education and information about fatigue, and strategies to reduce its effects either via a self-directed method, or professionally led with a home visit and telephone support. Baseline data will be collected prior to randomisation, and further data will be collected at 2- and 6-weeks post intervention.

**Discussion:**

To our knowledge this is the first randomised controlled trial of a program which compares the efficacy of a self-management approach and health professional assistance for the management of fatigue in the early post-partum period. If effective, it could offer an important, universal public health management approach to this common health concern.

**Trial registration number:**

Australian New Zealand Clinical Trials Registry, ACTRN12611000133932.

## Background

The experience of fatigue and exhaustion is a common health concern for parents, particularly those with young infants
[1,2]. Emerging research suggests that fatigue is associated with parent mental health and wellbeing difficulties
[3-5], as well as a range of adverse parenting behaviours
[3,6,7]. Given that fatigue may have implications for parents’ functioning, there is a need for interventions to support parents to manage experiences of fatigue and exhaustion during the post-partum period. This paper presents the study protocol of a randomised controlled trial of a universal parenting program, *Wide Awake Parenting (WAP)* designed to assist with the management of fatigue and improve parent wellbeing.

The terms tiredness, fatigue and exhaustion are often used interchangeably by parents, and in the research literature. While tiredness is transient, fatigue refers to persistent exhaustion and lack of energy that is not easily relieved by rest or sleep
[8]. For the purpose of this paper, the terms fatigue and exhaustion will be used interchangeably. In a qualitative study by Herbert
[9], fatigue was found to be a significant health concern that emerged during the first few days following birth and remained at 3-months post-partum. Additional quantitative studies have also found fatigue to be one of the most commonly reported health concerns during the early post-partum period
[1,2,10,11], and as many as 67% of Australian mothers report persistent tiredness at 6-months post-partum
[12]. Although previous studies have typically focused on fatigue in mothers, emerging research highlights that fathers experience similar levels of fatigue as mothers
[13,14] and that fatigue is a common experience for many fathers during the early parenting period
[15].

There are a variety of reasons why parents of infants may become fatigued or exhausted. Pugh and Milligan
[16] proposed a model of childbearing fatigue being influenced by physiological, psychological, and situational factors that may put a parent at risk of exhaustion and interfere with daily functioning. Research has found that birth-related factors such as breastfeeding
[17,18] and caesarean delivery
[19], as well as demographic and family characteristics including older maternal age
[20,21], sole parenting
[3,21] and low income
[22] to be associated with fatigue in parents. Additionally, during late pregnancy and the post-partum period, parents experience significant changes in their sleep patterns, including less night-time sleep and more disrupted sleep, which may contribute to feelings of exhaustion
[13,14,23]. Parents with infants who frequently wake at night are at risk of experiencing clinically significant levels of fatigue and exhaustion
[24].

Furthermore, recent Australian research on fatigue in the early parenting period suggests that fatigue can last well beyond infancy
[3]. This study found that a variety of socio-ecological factors place mothers and fathers at increased risk of experiencing fatigue, including poor sleep quality, insufficient social support, poor diet and exercise, ineffective coping styles, sleep quality and child temperament
[3].

### Effects of fatigue on parent wellbeing and behaviour

The experience of fatigue, while often anticipated, is largely under-prepared for by new parents
[9]. Fatigue not only has the potential to interfere with how parents adjust to their new role as a mother or father, but also for the resumption of previous roles and responsibilities, including those in paid work, social and family settings
[1,16,25]. It is well documented that fatigue can impair daily functioning
[24], social judgment and cognitive functioning, such as memory, decision-making, concentration and planning
[26-29]. The same is true for parents. In a study of 109 Australian mothers attending a public mothercraft unit, mothers who were clinically exhausted were found to experience significant impairments in their daytime functioning and reduced clarity of thought
[24].

Fatigue is likely to impact parental wellbeing. A study by Bayer et al.
[30] found that maternal tiredness in a community sample of Australian mothers with infants (3-6months) was associated with poorer mental and physical health, including symptoms of depression, anxiety, stress and fatigue/energy. The array of extra demands placed on parents along with the experience of fatigue is likely to add to parental stress and decrease mood
[31]. Although fatigue and loss of energy are part of the diagnostic criteria for clinical depression it has been found that the two are separate, distinct, unique psychological constructs
[13,32-35]. Fatigue has been found to be strongly related to symptoms of depression and anxiety during the prenatal
[1,36] and postnatal period
[33,37,38]. It is likely that the two conditions exacerbate each other
[21]; fatigue can heighten feelings of depression, anxiety and helplessness, which in turn leads to further exhaustion
[36].

It is also likely that fatigue adversely affects parenting practices and experiences. Emerging research suggests that fatigue can increase parenting stress
[3,6,39], limit patience in coping with infant crying
[39], and decrease parenting confidence, satisfaction and self-efficacy
[3,6,7]. Recent Australian research shows that mothers and fathers who are fatigued are using more irritable, frustrated and impatient parenting behaviours directed towards their child
[3]. Studies also show that fatigued parents are less warm and are less likely to be involved with their child
[3,7,40]. Not surprisingly, fatigue has the potential to impact upon parents’ ability to care for and interact with their infant or child
[4,30].

Given that fatigue can adversely affect the ability to parent optimally, it also has the potential to influence child outcomes and development
[41]. Parks et al.
[2] found an association between mothers reporting persistent fatigue at 18 months post-partum and poorer eye-hand performance in their infants. While research in this area is limited, associations have also been found for other wellbeing difficulties. For example, Kahn, Zuckerman, Bauchner, Homer and Wise
[42] found that depression in mothers was associated with poorer physical health and increased behaviour problems in their children at age three.

Fatigue plausibly presents a negative cycle for parents; parents who feel tired may not sustain self-care behaviours; they then may become ill, which in turn may influence their ability to get enough sleep and rest as they deal with daily demands; resulting in more fatigue
[2]. Fatigue can also result in increased conflict between partners
[30] and can have a detrimental impact upon family relationships and family functioning
[25]. The relationships between parental fatigue, parenting and child development described above are also likely to be complex and bi-directional. Reducing or preventing one wellbeing difficulty, such as fatigue, may have a multitude of benefits on other aspects of a parent’s life.

### Current interventions and management of fatigue

With growing evidence suggesting that fatigue is a serious health and wellbeing concern for many parents, little research has been conducted on strategies to manage and reduce parental fatigue. Research identifies the need for psycho-education about the effects of fatigue and strategies to promote self-care behaviour to conserve energy, improve quality of diet, increase exercise, reduce daily demands, maintain regular sleep routines, and allowing time for rest
[2,4,43]. Although a common experience for many new parents and a topic parents would like to discuss more
[12], mothers have reported feeling that it is inappropriate to seek professional support for their fatigue and it is often minimised or overlooked by health professionals
[10].

A randomised control study of a self-care intervention to reduce fatigue in a sample of 68 first-time mothers was conducted by Troy and Dalagas-Pelish
[44]. Mothers were given a *Tiredness Management Guide* which described eight potential sources of post-partum fatigue, including infection, lack of daytime rest, pressure to get everything done, interruption in night-time sleep, pain, stress, anaemia and social activities. The guide listed several techniques for each source of fatigue and asked mothers to try some of the suggestions whenever they felt tired. Mothers completed the intervention over a four week period from two weeks post-partum to six weeks post-partum. Results revealed whilst the use of the self-directed intervention reduced morning fatigue at the fourth week post-partum, overall the intervention was not associated with a significant decrease in fatigue from the second week to the sixth week post-partum as compared to mothers in the control group.

A more promising intervention was trialed by Thome and Alder
[33]. Their randomised control study investigated the use of a telephone intervention to reduce symptoms of fatigue. Seventy-six mothers of behaviourally difficult 2-3 month old infants participated in the study. The intervention commenced when infants were 4-6months, lasting approximately two months in duration, where each mother received five telephone calls from a registered nurse. The intervention was based on cognitive-behavioural techniques and information and advice was given on topics related to maternal distress (e.g., fatigue, health problems, role conflict) and infant behaviours (e.g., sleep, crying, feeding and health problems). Results revealed that mothers who received the telephone intervention had a significant reduction in fatigue over time than those mothers in the control condition. This intervention may prove to be effective in managing symptoms of fatigue in parents as they receive one-on-one support from a trained health professional, allowing them a context to discuss and obtain additional information and strategies that are tailored to their specific needs. The results from the control group show that if nothing was done to relive maternal fatigue, it did not decrease overtime, suggesting that mothers need specific and targeted interventions to combat fatigue. Whilst this appears to be evidence for the treatment of fatigue, mothers in this sample were approached to participate as they had reported having a difficult baby in a previous study, these findings may not be generalizable to a community sample of parents.

Taken together the findings from the existing interventions above suggest that a parent-led, self-directed intervention may not be effective in preventing or managing post-partum fatigue. There is promising evidence however, that short-term, direct support from a health care professional may be beneficial in reducing the symptoms of parental fatigue.

### Development of Wide Awake Parenting

Research suggests that reducing daily demands, improving quality of diet and exercise, maintaining a regular sleep routine, promoting realistic parenting expectations, and encouraging help-seeking, can be useful for the management of fatigue
[2,4,43]. Similar strategies were reported to be beneficial by parents of young children aged 0-6 years attending focus groups
[45,46]. WAP was developed as a psycho-educational program based on evidence about factors associated with fatigue and strategies for the management of fatigue, as outlined above.

A preliminary study evaluating the content of WAP was conducted with 49 parents of young children aged 0-4 years attending a residential program for sleep and settling problems
[47]. The program was delivered in the form of brief 90-minute workshop that provided psycho-education about fatigue and the potential impact of fatigue on parenting and wellbeing. Practical strategies to recharge and save energy were offered. These included taking time out for self, prioritising, problem solving, getting support, challenging unhelpful thinking, diet and exercise, and sleep hygiene. The program was found to have short-term effects on strengthening parents’ self-efficacy, their intention to engage in self-care behaviours, parents’ beliefs about the importance of self-care and perceived expectations of the benefits from managing fatigue. In addition to the short-term effects, the program was found to be acceptable and relevant to the needs of parents. The results of this pilot therefore provide encouraging support for the use of a psycho-educational based program for the management of parent fatigue in the post-partum period.

The aim of this paper is to present the study protocol for a randomised controlled trial of a psycho-educational intervention, WAP. The aim of WAP is to reduce fatigue, and promote parents’ well-being during the early post-partum period in a self-selected, community sample of parents. The content and development of WAP has been published elsewhere
[47]. The recruitment phase of this trial is currently complete, with intervention delivery and data collection ongoing.

## Method/design

### Study design

Randomised controlled trial.

### Ethics approval

Approvals were obtained from the Parenting Research Centre Human Research Ethics Committee and the Department of Early Education and Early Childhood Development, Early Childhood Research Committee.

### Setting

Seven Melbourne (state of Victoria, Australia) Local Government Areas (LGAs; Wyndham, Stonnington, Glen Eira, Darebin, Whitehorse, Greater Dandenong and Casey) were chosen for recruitment given the high birth rates per annum reported in 2008
[48]. Within each LGA, parents were recruited through Maternal and Child Health services (MCHNs) and early childhood immunisation sessions. MCHNs provide a universal, free service offered to all Victorian families with scheduled family visits (covering 93% of all births) from the post-partum and up to 42 months of age. MCHNs run a range of individual, family and group services to families with infants and pre-school aged children (<6 years of age), including “new parent” education groups for first-time parents, aimed at providing parenting information and support. Free, universally accessible early childhood immunisations are provided in Australia, under the National Immunisation Program, via MCHNs in regular centre-based sessions. In two of the participating LGA’s, immunisation services are provided by the Environmental Health Unit (Casey and Wyndham) and not the MCHNs.

### Participants

#### Inclusion criteria

Mothers and fathers of infants aged 0-6 months, seen by their MCHN, attending an immunisation session or “new parent” group in one of the seven participating LGAs were eligible to participate in the study.

At the routine visits, participating MCHNs provided eligible parents’ with a flyer containing information about the study so that they could contact the research team, or gained permission to pass on the parent’s contact details to the research team on parents behalf. The study team contacted interested parents to provide further verbal information about the study. Participant information and consent forms were sent to parents who were willing to participate, and for partnered parents, a separate information and consent form for partners was also sent.

At immunisation sessions and “new parent” groups, the research team approached parents to ascertain their eligibility and to provide them with verbal and written information about the research. Contact details for interested parents were obtained, and parents and their partners were provided hard copies of the participant information and consent forms, either by post, or in person.

#### Exclusion criteria

Parents were excluded from the study if they were under the age of 18 years, had a child over the age of six months at the time of being approached to participate, were living outside one of the seven LGAs or had insufficient English to complete the questionnaires.

### Sample size/power calculation

Power analysis using the program 'GPower 3.1.2' was conducted to determine the required sample size for the study. A 3-group comparative study would require a total sample of 184 participants (approximately 61 parents in each treatment condition) to have 80% power to detect a statistically significant finding at *p* < .05 and a moderate effect size for the short-term outcomes at two weeks post-intervention. Allowing for a 20% dropout rate, we aimed to recruit approximately 221 parents (approximately 74 participants in each treatment condition).

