### Randomisation

Families were randomised upon receipt of their signed consent form and baseline questionnaire. Prior to the recruitment period, a computer generated random number sequence provided by
http://www.random.org was established for each participating LGA. This allowed for each parent or family (if both parents participated) per LGA to have equal chance of being allocated to either of the intervention conditions (i.e., written information with telephone support or written information only) or control condition. The research team and families remained blind to group allocation at the time of recruitment and consent. However, following the return of the participants consent form, knowledge of group allocation is unavoidable given the type of intervention. Thus, each parent or family were allocated to one of the intervention or control conditions and notified of this allocation.

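### The 20% dropout allowance multiplies 184 by 1.2 instead of dividing by 0.8, so the recruitment target of 221 covers only about 16.7% dropout

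*Protocol article*

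**What the plan says.** All the figures stand in one paragraph of the Protocol article, Sample size/power calculation. A three-group comparison "would require a total sample of 184 participants (approximately 61 parents in each treatment condition"). The power attached to that number is 80%, at the 5% level. The target effect is described as "a moderate effect size for the short-term outcomes at two weeks post-intervention"; the paragraph gives no number for it and does not name the test entered in GPower.

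The next sentence inflates for attrition: "Allowing for a 20% dropout rate, we aimed to recruit approximately 221 parents (approximately 74 participants in each treatment condition").

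Under Randomisation, each parent or family is "to have equal chance of being allocated to either of the intervention conditions" or the control condition, so equal arms can be assumed. No other section gives a different dropout rate, recruitment target or inflation rule.

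Two further points bear on the consequence. The last paragraph before Method/design (under Development of Wide Awake Parenting) reports that recruitment has finished while data collection continues. Data analysis plans a split-plot ANOVA and an intention-to-treat analysis in which missing later values are filled by last observation carried forward (LOCF).

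**The concern.** The paragraph treats 184 as the number to be left after losses and 20% as the loss to be covered. A dropout rate is a fraction of those who enter, so the number to recruit is the required number divided by the fraction retained. The stated target is instead the required number plus a fifth of itself, which is always too small.

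Three of the paragraph's figures (221 recruited, 20% lost, 184 left) therefore cannot all be true. Readers will use this paragraph to judge whether the trial reached its planned size and how to read a null result. As it stands, they would believe that a 20% loss was provided for when it was not.

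**Working it through.** **Inputs** (Sample size/power calculation): required total N = 184, about 61 per arm; dropout d = 0.20; recruitment target 221, about 74 per arm. Three arms with equal allocation (Randomisation).

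**1. Reproduce the stated target.**
- N × (1 + d) = 184 × 1.2 = 220.8, rounded to 221.
- Per arm: 221/3 = 73.7, rounded to 74.

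Both stated figures are reproduced, so the rule that was used is clear.

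**2. Apply the rule that keeps 184.**
- N / (1 − d) = 184/0.8 = 230.
- Per arm: 230/3 = 76.7, about 77.
- Difference from the stated target: 230 − 221 = 9 recruits, or 9/230 = 3.9%.

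**3. What 221 delivers at 20% dropout.**
- 221 × 0.8 = 176.8, about 177 with observed follow-up; 176.8/3 = 58.9, about 59 per arm.
- Shortfall: 184 − 177 = 7.
- Counting the target as 3 × 74 = 222 gives 222 × 0.8 = 177.6, still short of 184.

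**4. Dropout that 221 can absorb.**
- 1 − 184/221 = 0.167, or 16.7%.
- For 222: 1 − 184/222 = 0.171, or 17.1%.

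**5. Power, as an illustration only.** Steps 1 to 4 need no effect size; this step does. Assume a three-group one-way ANOVA at 5%, with 2 and N − 3 degrees of freedom and noncentrality N × f².

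| Assumed f | Power at N = 184 | Power at N = 177 |
|---|---|---|
| 0.231 (solved so that 184 gives exactly 80%) | 80.0% | 78.3% |
| 0.25 (conventional medium f) | 86.3% | 84.8% |

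The solved f = 0.231 corresponds to η² = f²/(1 + f²) = 0.051, below the 0.06 that Data analysis calls medium. With f = 0.25 this test would need only 158 parents for 80%, not 184. So the test and effect size behind 184 cannot be recovered from the article, and the power at 177 cannot be fixed from it either. In both rows the loss is between 1 and 2 percentage points.

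**The case against.** **The targets are called approximate.** That word does not cover the gap. 221 is the rounded product of 184 and 1.2, and taking 222 instead still leaves fewer than 184.

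**LOCF keeps everyone in the analysis.** This stands in part. Families are randomised only once the baseline questionnaire is in, so every randomised parent has a value to carry forward, and the intention-to-treat set would be about 221 if the target was met. It would be wrong to say that only 177 parents are evaluable; 177 is the number with observed follow-up. But carried-forward values do not restore the lost information. The paragraph itself treats dropout as a loss to be offset by extra recruitment, so LOCF does not justify the 1.2 multiplier.

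**The consequence is small and recruitment is over.** This stands. The gap is 9 recruits in 230. No estimand, comparison, analysis method or type I error changes, and no design decision remains open.

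**A reader might infer that the trial falls below 80% power.** The documents do not support this. It follows only if 184 gives exactly 80%; at f = 0.25 in a one-way ANOVA, power at 177 is still about 85%. A reader might also take a pairwise contrast at d = 0.5, find 76.8% with 59 per arm, and blame the inflation step for the whole distance from 80%. But 61 per arm, before any dropout, already gives only 78.2% for that contrast. The dropout step accounts for 78.2 − 76.8 = 1.4 points, so the pairwise figure is no measure of this error.

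**Conclusion.** The stated figures contradict each other. A target of 221 does not allow for 20% dropout from a requirement of 184; it allows for about 16.7%. At 20% dropout about 177 parents (59 per arm) would have observed follow-up, 7 short of 184, and a full 20% allowance would have been 230. This takes the plan's own 184 and 20% as given and rests on no assumption about test or effect size.

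The effect on power is modest, and its level is not established: about 78% at 177 is conditional on 184 giving exactly 80% in a three-group one-way ANOVA. A loss of the 80% target is not shown. This is a minor correction to a stated figure and not a defect in the design.

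**What to change.** Correct the sentence on dropout wherever the sample size is reported. Suggested wording:

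> Recruiting 221 parents retains 184 with observed follow-up at up to 16.7% dropout. At 20% dropout about 177 (59 per arm) remain; a full 20% allowance would have been 230.

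If a power figure for 177 is wanted, recompute it from the inputs originally entered in GPower and name the test and numerical effect size beside it. Do not insert the 78% illustration as the trial's power.

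The cost is one or two sentences and one rerun of the existing calculation. No further parents are needed, and neither conduct nor analysis changes. The only loss is that the stated cover falls from 20% to 16.7%. As data collection was still under way when the article was written, the corrected statement can go into the results report.
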